### Interim analyses {21b}

Not applicable since no interim analyses are planned.

### Methods for additional analyses (e.g., subgroup analyses) {20b}

Not applicable since no additional analyses such as subgroup analyses are planned.

### Methods in analysis to handle protocol non-adherence and any statistical methods to handle missing data {20c}

Statistical analyses will be carried out according to the intention-to-treat approach and therefore will include all randomized participants. The extent of missing data will be analyzed. We will explore missing data patterns and determine the type of missing data (missing completely at random, missing at random, not missing at random). We will use multiple imputation to substitute missing values and will conduct sensitivity analyses for both the datasets with and without the imputed data.

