### Sample size {14}

To specify the sample size needed for the different analyses, we conducted a power analysis based on a probability level of 0.05 and a power of 0.80 with G*Power [53] for a repeated-measures ANOVA with a within-between-interaction. To test the efficacy of the self-help program compared to the control condition, we expected a small-to-medium between group effect size of *d* = 0.35 and a correlation between the factors of at least *r* = 0.4. The expected effect size is based on the results of meta-analyses on the effectiveness of unguided internet-based self-help programs targeting depressive symptoms [17, 54]. We decided to base the expected effect size on unguided internet-based self-help programs as it is yet to be determined if a guidance on demand approach yields higher effect sizes than unguided self-help [23, 24] . Power analysis indicated a necessary sample size of 80 individuals. In consideration of a possible attrition rate between 5.4 and 45.5% at post-assessment, we aim to recruit between 80 and 120 participants at baseline [17].

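### The missing-data section promises to establish whether data are MAR or MNAR, which observed data cannot show, and the one sensitivity comparison it names cannot test departures from MAR

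*Protocol article*

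**What the plan says.** Three statements in the protocol article bear on this.

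- Section {20c}, on non-adherence and missing data, sets the population: "Statistical analyses will be carried out according to the intention-to-treat approach and therefore will include all randomized participants". It then says that missing-data patterns will be explored and that the team will "determine the type of missing data (missing completely at random, missing at random, not missing at random". All three mechanisms are listed as possible results.
- The same section continues: "We will use multiple imputation to substitute missing values and will conduct sensitivity analyses for both the datasets with and without the imputed data". The imputation is not made conditional on which mechanism is found.
- Sample size {14} allows for a "possible attrition rate between 5.4 and 45.5% at post-assessment", taken from one of the cited meta-analyses, and on that basis says "we aim to recruit between 80 and 120 participants at baseline".

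The 3-week assessment is the time point of the superiority comparison (Trial design {8}). The primary model in {20a} is a mixed model on the baseline and 3-week scores only.

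**The concern.** Whether data are MAR or MNAR depends on the values that were not seen. No pattern analysis or test on the observed values can settle it. A section that lists MNAR as a possible result promises something that cannot be delivered, and a later report that the data were found to be MAR would have no basis.

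The named sensitivity comparison does not fill the gap. A likelihood-based mixed model without imputation assumes MAR, and so does standard multiple imputation. A complete-case analysis assumes as much or more. If the two results agree, that may be read as robustness to dropout, although neither analysis could have revealed an MNAR problem. The outcome is self-reported and participants know their allocation ({17a}), so outcome-related non-response cannot be excluded. With an assumed effect of only d = 0.35, a moderate bias would change the interpretation.

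**Working it through.** **Inputs.** From Sample size {14}: d = 0.35, correlation 0.4, alpha 0.05, power 0.80, N = 80, recruitment 80 to 120, attrition 5.4% to 45.5%. From {16b}: allocation follows a completed baseline assessment, so in the primary analysis the data at risk are the 3-week scores.

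**The plan's own figure.** For a repeated-measures ANOVA interaction with two groups and two time points, take f = d/2 = 0.175. Then lambda = f² × N × m/(1 − r) = 0.030625 × 80 × 2/0.6 = 8.17, with 1 and 78 degrees of freedom. Power is 0.806, so N = 80 reproduces. It is used here only to fix d = 0.35 as the scale.

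**Participants with 3-week data at the upper attrition figure.** 80 × (1 − 0.455) = 43.6 and 120 × (1 − 0.455) = 65.4, so about 44 to 65.

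**Why MAR and MNAR cannot be separated.** Let x be everything recorded (arm, baseline, usage) and let delta be the amount by which the mean 3-week score of non-responders differs from that of responders with the same x. MAR implies delta = 0; any other delta is MNAR. Every value of delta gives the same likelihood for the observed data, because delta concerns only unobserved scores. Comparing the baseline of responders and non-responders can contradict MCAR. It carries no information on delta.

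**Effect of a non-zero delta.** If only intervention-arm non-responders are worse than MAR predicts, by delta SD, and a is the fraction missing in that arm, then bias = a × delta. The range for delta is an assumption.

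| a | bias at delta = 0.2 | bias at delta = 1.0 | delta that brings 0.35 to zero (0.35/a) |
|---|---|---|---|
| 5.4% | 0.011 | 0.054 | 6.48 SD |
| 45.5% | 0.091 | 0.455 | 0.77 SD |

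The last column is where the point estimate reaches zero, not where significance is lost.

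**Control-like dropouts (illustration).** This is delta = 0.35, so the effect is 0.35 × (1 − a):
- a = 5.4%: 0.35 × 0.946 = 0.33
- a = 45.5%: 0.35 × 0.545 = 0.19

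**Would the named comparison show it?** A simulation used N = 120, 1,000 repetitions per rate, a true effect of zero, equal missingness in both arms, and delta = 0.5 SD in the intervention arm only. A baseline-adjusted regression on observed data was compared with 20 MAR imputations. Negative values are an apparent benefit. The 20% row is an assumed intermediate rate.

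| missing | expected bias (a × 0.5) | observed data only | imputed |
|---|---|---|---|
| 5.4% | 0.027 | −0.023 | −0.023 |
| 20% | 0.100 | −0.110 | −0.111 |
| 45.5% | 0.228 | −0.231 | −0.229 |

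At 45.5% both analyses are off by about 0.23 SD, yet within a trial they differ by only 0.03 SD on average.

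**The case against.** The strongest reply has five parts.

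- *The faulty step drives nothing.* Multiple imputation is planned whatever mechanism is found, so the step does not itself bias the estimate. This stands. It limits the harm to what would be claimed about the mechanism.
- *The text does not say that the with/without contrast is the only sensitivity analysis.* It names the datasets on which such analyses will be run, and an unseen analysis plan may add an MNAR method. This also stands: a reader might infer that no MNAR check exists anywhere, and the document cannot show that. But no analysis plan can make the mechanism identifiable, and the comparison that is named cannot test MAR.
- *Nothing shows that dropout will be MNAR.* A reader might infer that intervention participants who do not benefit will stop answering, so that the effect will be overstated. The document does not support that. Section {18b} asks everyone for every questionnaire whatever their adherence, with two reminders. Improved participants may also stop answering, and waiting-arm dropout may be informative too.
- *45.5% is the top of a planning range*, neither an expected rate nor an intervention-arm rate. At 5.4% the illustration moves 0.35 only to 0.33. This stands.
- *The agreement in the simulation is built in*, because no auxiliary variables were used. That is fair; it demonstrates the point rather than providing evidence about this trial. If programme-usage data ({18a}) entered the imputation, the two analyses could differ, and that would be informative about missingness tied to usage. It would still not test MNAR.

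**Conclusion.** The point holds in two limited parts. First, the commitment to establish the mechanism is wrong as written, because MAR and MNAR cannot be told apart from the observed data. Second, agreement between results with and without imputed values would not show robustness to MNAR dropout, since both rest on MAR or stricter assumptions.

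The practical size runs from negligible to substantial over the protocol's own attrition range. The 0.33 and 0.19 rest on three assumptions: an MAR estimate of exactly 0.35, control-like outcomes in all intervention dropouts, and the quoted attrition applying to that arm. They illustrate sensitivity and do not predict bias. The trial is not invalidated; what lacks support is any robustness claim drawn from the named comparison alone.

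**What to change.** In {20c}, replace the promise to establish the mechanism with a statement that patterns and predictors of missingness will be explored and that the primary analysis assumes MAR. Keep the with/without comparison, which can show sensitivity to the imputation model, and add one prespecified MNAR sensitivity analysis of the 3-week PHQ-9: either a delta-adjusted tipping point or reference-based imputation from the control arm. Which variables enter the imputation model can stay in the analysis plan.

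The cost is some rewording and a little more analysis work, with no new data. At this version recruitment was still open (N = 99 in January 2021, Trial status) and no interim analysis was planned ({21b}), so the addition could be fixed before any outcome analysis.

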### Plans to give access to the full protocol, participant level-data, and statistical code {31c}

There are no plans for granting public access to the full protocol, participant-level dataset, and statistical code.

### Composition of the data monitoring committee, its role and reporting structure {21a}

As to the best of our knowledge, the internet-based self-help program in itself does not bear risks for the participants. Therefore, a data monitoring committee is not required. The principal investigator, the co-principal investigator and the PhD students warrant for data and participant safety.

### Adverse event reporting and harms {22}

In this trial, adverse events are defined as unintended negative developments in the participants, which may occur at the time of the use of the internet-based self-help program, but do not have to be causally related to its use. Those unintended negative developments in the participants include acute suicidality and hospitalization. Such adverse events and the corresponding actions taken will be documented in the case report form.

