### Criteria for discontinuing or modifying allocated interventions {11b}

Since internet-based self-help is not suited as a treatment for acute suicidality, participants reporting an acute crisis during treatment are referred to an appropriate treatment. This will be recorded and reported as an adverse event.

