##### Suicide Behavior Questionnaire Revised (SBQ-R)

The SBQ-R assesses suicidal experiences and behavior [28]. The SBQ-R consists of 4 items which are not scaled equally. A total score of the 4 items is calculated. The total score can range from 3 to 18 whereas a score greater than or equal to 8 is considered the most useful cutoff score for suicide risk in a clinical sample [28]. This SBQ-R cutoff is also used as an indication for suicidal tendencies (safety outcome). The internal consistency of the SBQ-R is satisfactory (Cronbach’s alpha = 0.72) [34].

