### Frequency and plans for auditing trial conduct {23}

The research management of the Faculty of Human Sciences at the University of Bern, an independent research control unit, warrants the auditing. There will be on site monitoring visits on a regular basis. The monitoring visits are documented in a monitoring report form. The data monitoring committee controls study procedures such as the site progress and enrollment, obtaining participant informed consent, randomization, or the reporting of adverse events.

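### The adverse event definition is tied to program use, so it does not secure equal counting in the waiting arm during weeks 0–3; the protocol also contradicts itself on a data monitoring committee

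*Protocol article*

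**What the plan says.** Under Adverse event reporting and harms {22}, adverse events are unintended negative developments "which may occur at the time of the use of the internet-based self-help program". No causal link to that use is needed. The section then gives examples: "Those unintended negative developments in the participants include acute suicidality and hospitalization". These events, and the action taken, are documented in the case report form.

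Under Criteria for discontinuing or modifying allocated interventions {11b}, "participants reporting an acute crisis during treatment are referred to an appropriate treatment. This will be recorded and reported as an adverse event".

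Trial design {8} opens the program to the waiting arm 3 weeks after baseline. The same section says the arms cannot be compared at the later follow-ups, because both will by then have used the program. Statistical methods {20a} restricts the primary analysis to baseline and week 3.

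On oversight, section {21a} reasons that the program carries no known risk and concludes: "Therefore, a data monitoring committee is not required". It makes the investigators and PhD students responsible for data and participant safety. Section {23} names the faculty's research management as the independent auditing unit, and then states: "The data monitoring committee controls study procedures such as the site progress and enrollment". The list in that sentence goes on to include adverse event reporting.

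**The concern.** A definition that requires no causal link is useful because events can be counted without anyone judging their cause. Such a count is informative mainly when set against the rate in a concurrent comparator. Here the time window is linked to using the program, which waiting participants cannot do in the randomised phase. Staff who follow the wording would log an admission to hospital in one arm and not in the other.

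Any table of adverse events by arm for weeks 0–3 would then reflect the recording rule as well as the event rates. It could make the program look worse than waiting, or hide a benefit. The protocol's premise that the program carries no risk could not be checked against these counts.

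The committee wording matters for a related reason. Checking of adverse event reporting is assigned to a body that another section says is not needed, so a reader cannot tell who does it.

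**Working it through.** The plan states no figure on this point, so the check sets the sections side by side.

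**Step 1. Who falls within the definition, and when (literal reading of {22}, access times from {8})**

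| Arm | Weeks 0–3 | Weeks 3–18 |
|---|---|---|
| Intervention | program available: hospitalisation or acute crisis during use counts | counts during use |
| Waiting | no program: the same event does not count | counts once the program is in use |

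The wording of {11b} gives the same result for an acute crisis, since it speaks of a crisis during treatment.

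**Step 2. Size of the window**

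- Share of the waiting arm's follow-up: 3/18 = 0.167, about 17%.
- Share of the period in which the arms can be compared: 3/3 = 100%.
- People affected, from 1:1 allocation {8} and a target of 80 to 120 {14}: 80/2 = 40 to 120/2 = 60.

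**Step 3. What other data cover the waiting arm in weeks 0–3**

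- *Worsening of depression.* The PHQ-9 is taken at baseline and week 3 in both arms ({12}, {20a}), and everyone is asked to complete every questionnaire {18b}. This is covered.
- *Suicidality.* The SBQ-R section makes a score of 8 or more a safety outcome, with no link to program use. It is covered at week 3 if the SBQ-R is scheduled then. The schedule is in Fig. 2, which is not shown, so this is an assumption.
- *Concomitant treatment.* Both arms report psychological or psychiatric treatment at each measurement {11d}. This may reveal some admissions, but it is not described as asking about them.
- *Hospitalisation.* No questionnaire described records it, so it depends on adverse event reporting.

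**Step 4. The committee**

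Section {21a} says a committee is not required. Section {23} describes one as controlling enrolment, consent, randomisation and adverse event reporting. Both are current text and they cannot both stand. The two sections name three candidates for the task: the investigators with the PhD students, the faculty research management, and the committee.

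**The case against.** The strongest reply is that the text is loose rather than exclusionary. The definition says events may occur at the time of use and refers to participants in general. Nothing states that waiting-arm events are left unrecorded. Section {11b} deals with discontinuing or modifying the intervention, so a reference to the treatment period is natural there and is only weak support. The case report form or full protocol, neither shown, may set a wider window. This stands as far as it goes: the gap follows from a literal reading. But the article states a rule instead of leaving one out, and followed as written the rule treats the arms differently.

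A reader might infer several stronger things that the protocol does not support:

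- *Harms in the waiting arm are never counted.* After week 3, waiting participants who use the program fall within the definition.
- *Deterioration while waiting is invisible.* The PHQ-9 at baseline and week 3 in both arms is the basis of the primary analysis, and the SBQ-R cutoff is already a safety outcome.
- *A planned comparison of harms is biased.* No between-arm comparison of adverse events is stated, only documentation.
- *The recorded waiting-arm rate will be zero.* That turns the strictest reading into a number; what staff actually recorded is not known.
- *Nobody oversees safety.* The investigators hold responsibility for participant safety, and an independent unit audits with regular visits. The committee reference may be a naming slip.

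It can also be said that leaving PHQ-9 deterioration and the SBQ-R cutoff out of the adverse event definition is a legitimate choice. That is accepted and is not part of this point.

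**Conclusion.** The point holds in a limited form. As worded, the definition does not secure equal counting of hospitalisations and acute crises in the two arms during weeks 0–3. This is about 17% of the waiting arm's follow-up but all of the randomised comparison period, for about 40 to 60 people. The remaining gap is clearest for hospitalisation. For suicidality it is partly closed by the SBQ-R, on the assumption that it is scheduled at week 3.

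The conclusion rests on reading the definition literally and on no wider window being set elsewhere. The contradiction between {21a} and {23} needs neither assumption. Neither matter touches the primary efficacy analysis, but both should be corrected before adverse events are reported.

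**What to change.** 1. Define adverse events as any such event from randomisation onward in both arms, regardless of program use, and align the wording of {11b} on what is recorded as an adverse event.
2. Report adverse events for weeks 0–3 by arm. Beside them, give the number per arm reaching the protocol's own SBQ-R cutoff of 8, if Fig. 2 schedules the SBQ-R at week 3.
3. Check what has been recorded so far for waiting participants in weeks 0–3, and state in the report where capture was incomplete.
4. Reconcile {21a} and {23} by naming the body that actually controls adverse event reporting.

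The cost is some rewording and one extra table. There is a limit to what this can repair. Trial status gives 99 enrolled in January 2021 against a target of at most 120, so hospitalisations that were not recorded for earlier waiting participants may be lost, and rewording will not recover them. An amendment may be needed; if it is judged substantial, {25} requires ethics committee approval before it takes effect.

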### Frequency and plans for auditing trial conduct {23}

The research management of the Faculty of Human Sciences at the University of Bern, an independent research control unit, warrants the auditing. There will be on site monitoring visits on a regular basis. The monitoring visits are documented in a monitoring report form. The data monitoring committee controls study procedures such as the site progress and enrollment, obtaining participant informed consent, randomization, or the reporting of adverse events.

### Plans for communicating important protocol amendments to relevant parties (e.g., trial participants, ethical committees) {25}

Important protocol amendments will be reported to the relevant parties (i.e., the Cantonal Ethics committee Bern, the trial participants and trial registries) by e-mail. Substantial amendments are only implemented after approval of the Cantonal Ethics committee Bern. All non-substantial amendments are communicated to the Cantonal Ethics committee Bern within the Annual Safety Report.

### Dissemination plans {31a}

Trial participants and the general population are informed about the results of the study by means of a results report.

## Discussion

The internet-based self-help program ROCO is, to the best of our knowledge, one of the first internet-based self-help programs specifically developed for the treatment of psychological distress due to the situation surrounding the COVID-19 pandemic. The results will give insight into the efficacy and acceptance of an internet-based self-help program in the context of COVID-19 pandemic-related psychological distress. Moreover, the results will contribute to the further adaption of the self-help program. In light of possible multiple waves and future pandemics, it is important to investigate the effectiveness of such psychological interventions as mental health resources might be strained.

Limitations of this study include that only short-term effects of the internet-based self-help program can be determined, since the waiting control condition already receives access to the self-help program after 3 weeks.

## Trial status

Trial start date: May 2020.

Currently recruiting (*N* = 99, January 2021).

Approximate date when recruitment will be completed: April 2021.

Version 3: 28. January 2021.

## Data Availability

The principal investigator, the co-principal investigator and the PhD students have access to the full data sets. All data collected is stored on a firewall-encrypted back-upped server of the University of Bern with strictly regulated access only for researchers directly involved in the study.

## Abbreviations

AjD: Adjustment disorder
BEI: Bern Embitterment Inventory
CAU: Care as usual
CBT: Cognitive behavioral therapy
CD-RISC: Connor-Davidson Resilience Scale
COVID-19: Coronavirus-19
CSQ-8: Client Satisfaction Questionnaire-8
DASS-21: Depression Anxiety Stress Scale
GSE: General Self-Efficacy Scale
LOT-R: Life Orientation Test Revised
PHQ-9: Patient Health Questionnaire
RCT: Randomized controlled trial
SARS: Severe acute respiratory syndrome
SBQ-R: Suicide Behavior Questionnaire Revised
SEK-27: Self-report measure for the assessment of emotion regulation skills
SF-12: 12-Item Short-Form Health Survey
SUS: System Usability Scale
ULS: UCLA Loneliness Scale
